## 1. Introduction

Osteonecrosis of the femoral head (ONFH) is a common hip disorder characterized by femoral head collapse, which can lead to secondary osteoarthritis, resulting in severe hip pain and functional limitations [1]. In most cases, intraosseous necrosis has already occurred at the time of diagnosis, making early detection difficult, and patients are often asymptomatic before femoral head collapse, with spontaneous reduction in the necrotic area being rare and larger lesions more likely to progress to collapse [1,2]. A national epidemiological survey conducted in 2004 estimated that approximately 11,400 patients with ONFH were treated annually in Japan, with approximately 2200 new cases diagnosed each year [3]. Once femoral head collapse occurs, patients develop pain and gait disturbance, ultimately leading to irreversible deterioration of hip joint function, and many patients with ONFH require surgical treatment, with more than half undergoing surgery within nine months of diagnosis [4]. Total hip arthroplasty (THA) is indicated in advanced stages with substantial joint destruction and provides excellent pain relief and functional outcomes; however, complications such as infection and dislocation can occur, and long-term mechanical loosening may necessitate revision surgery [1,5,6]. Moreover, several studies have suggested that patients with ONFH may experience higher complication and revision rates after THA compared with those with primary osteoarthritis [7,8,9]. Because ONFH often affects relatively younger patients, the indication for THA should be considered carefully, and joint-preserving procedures are preferred before substantial joint destruction occurs [5,10]. Femoral osteotomy procedures, such as transtrochanteric rotational osteotomy and curved varus osteotomy, have been widely performed in Japan to transfer the viable portion of the femoral head to the weight-bearing area while shifting the necrotic region away from load-bearing zones [11,12]. However, these procedures are highly invasive, involving substantial disruption to bone, musculotendinous structures, and the joint capsule, and their utilization has shown a decreasing trend based on a Japanese nationwide database study [13].

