**Secondary outcomes**

The secondary outcomes will include the following:(1)Radiographic progression assessed at 3, 6, and 12 months using the same classification system(2)Changes in collapse length (mm) measured on serial radiographs at baseline, 3, 6, and 12 months(3)Clinical outcomes, including Harris Hip Score (HHS) and Japanese Orthopaedic Association Hip-Disease Evaluation Questionnaire (JHEQ), evaluated at baseline, 3 months, and 12 months(4)Bone remodeling of the grafted area assessed using computed tomography (CT) before surgery and at 3 and 12 months postoperatively.

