Continuous variables will be expressed as mean ± standard deviation or median (interquartile range), as appropriate, and categorical variables as frequencies and percentages. The primary outcome (progression of ONFH within 1 year) will be compared between the intervention group and the historical control group. To reduce confounding due to the non-randomized design, propensity score matching will be performed. The propensity score will be estimated using a logistic regression model including age, sex, body mass index, disease stage, disease type, and etiology of ONFH. Information regarding corticosteroid use, alcohol consumption, concomitant medications, and year of diagnosis will also be collected. Because of the limited sample size and exploratory nature of this pilot study, these variables will not be included in the primary propensity score model to avoid overfitting but will be described and considered when interpreting the results. Patients will be matched 1:1 using nearest-neighbor matching with a caliper width of 0.2 times the standard deviation of the propensity score. Patients for whom an adequate match cannot be identified will be excluded from the matched analysis. This may reduce the effective sample size and limit the generalizability of the findings. Covariate balance after matching will be assessed using standardized mean differences, with values < 0.1 indicating adequate balance. After matching, paired categorical variables, including the primary outcome, will be analyzed using McNemar’s test. Secondary outcomes will be analyzed descriptively and compared between groups using appropriate statistical methods. Missing data will be handled using complete case analysis. Because the historical control cohort is derived from institutional databases with routinely collected clinical and imaging records, the amount of missing data is expected to be minimal. Therefore, complete case analysis was considered appropriate for this exploratory study. Because the amount of missing data is expected to be minimal, formal sensitivity analyses or multiple imputation procedures are not planned. Alternative approaches to missing data will be considered in future confirmatory studies if necessary. All statistical analyses will be performed using JMP version 19.0 (SAS Institute, Cary, NC, USA). A two-sided *p*-value < 0.05 will be considered statistically significant.

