This study has several strengths. It evaluates a novel combined technique that addresses both intraosseous and intra-articular pathology. In addition, the externally controlled design with propensity score matching allows for adjustment of baseline differences between groups, improving the validity of comparisons. Furthermore, both radiographic and clinical outcomes are assessed, enabling a comprehensive evaluation of treatment effectiveness. However, several limitations should be acknowledged. First, this is a single-center study with a relatively small sample size, as this trial was designed as a pilot study, which may limit generalizability. Second, the use of a historical control group introduces potential selection bias and residual confounding, despite statistical adjustment. In particular, differences in treatment indications and clinical practice over time may have influenced the outcomes. Baseline is defined as the time of surgery in the intervention group and the time of initial diagnosis in the historical control group. This asymmetry may introduce bias because disease progression occurring before surgery in the intervention group is not captured. Furthermore, residual confounding due to unmeasured factors, including corticosteroid use, alcohol consumption, symptom duration, and temporal changes in clinical practice, cannot be completely excluded. In addition, baseline patient-reported outcome measures, including the HHS and JHEQ, are not available for the historical control cohort. Therefore, these outcomes will be evaluated descriptively within the intervention group, and direct comparisons between groups will not be possible. Third, the follow-up period is limited to short-term outcomes, and long-term durability, including prevention of femoral head collapse and conversion to total hip arthroplasty, remains unclear. In addition, the collapse length measurement used in this study has not been formally validated, and intra- and inter-observer reliability were not assessed. Therefore, measurement variability may influence the reproducibility of radiographic outcomes. Finally, variability in surgical technique and patient characteristics may influence the results. Therefore, caution is required when generalizing the findings to other populations and clinical settings. In conclusion, this study is expected to provide important preliminary evidence regarding the feasibility and potential effectiveness of arthroscopy-assisted core decompression combined with OCP/Gel implantation. The findings may contribute to the development of improved joint-preserving strategies for ONFH and support future large-scale prospective studies. This approach may offer a practical and scalable alternative to more complex regenerative therapies.

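### Complete-case analysis removes hips converted to THA from the 12-month collapse-length comparison, and section 2.10 promises group comparisons that not all secondary outcomes allow

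*Protocol article*

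**What the plan says.** Section 2.6 makes conversion to THA one of the two events that count as progression in the primary outcome. The same section defines collapse length as a distance between the contour of the femoral head and a sphere fitted to it.

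The secondary outcomes are radiographic progression; "Changes in collapse length (mm) measured on serial radiographs at baseline, 3, 6, and 12 months"; HHS and JHEQ, "evaluated at baseline, 3 months, and 12 months"; and CT remodeling of the grafted area.

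For all four, section 2.10 gives one rule: "Secondary outcomes will be analyzed descriptively and compared between groups using appropriate statistical methods". It adds: "Missing data will be handled using complete case analysis". It justifies this by expecting few missing values, because the historical data come from routine records, and it rules out sensitivity analyses and multiple imputation.

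The Discussion (section 3) notes that baseline HHS and JHEQ "are not available for the historical control cohort" and concludes that "these outcomes will be evaluated descriptively within the intervention group, and direct comparisons between groups will not be possible".

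**The concern.** Two things do not fit together.

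First, a hip that has been replaced has no femoral head contour to measure. Its 12-month collapse length is not a value that someone failed to record. It cannot exist, and the reason is that the hip failed. The argument that routine records are nearly complete does not reach such values. Complete-case analysis then compares only the hips that kept their femoral head, while the primary outcome counts the others as progression. Two outcomes meant to describe the same disease course would rest on different sets of hips, selected by the outcome itself.

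Second, the blanket promise of group comparisons in section 2.10 cannot be kept for HHS and JHEQ, as the Discussion says, nor for CT of a graft that conservatively treated controls never received.

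Collapse length is the only continuous radiographic measure among the secondary outcomes that can be compared between groups. Section 2.10 says that the study's estimates will feed sample-size calculations for later trials, so a selected estimate would be carried forward.

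**Working it through.** The protocol states no THA rate, standard deviation or expected collapse, so there is no figure of its own to reproduce. The first two steps compare the text. The third is an illustration on assumed inputs.

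**Step 1. What happens to a converted hip under the stated rules.**
- Primary outcome (section 2.6): counted as an event.
- Collapse length at 12 months (section 2.6): not measurable.
- Missing-data rule (section 2.10): complete case, so the hip is left out. No sensitivity analysis shows the effect.
- Values at 3 and 6 months may exist if conversion came later, but the 12-month value is lost.

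**Step 2. Which secondary outcomes can be compared between groups.**

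| Outcome | Available in historical controls? | Source |
|---|---|---|
| Radiographic progression | Nothing in the text rules it out | 2.6, 2.10 |
| Collapse length | Nothing in the text rules it out | 2.6, 2.10 |
| HHS, JHEQ | No, baseline scores are absent | Discussion |
| CT of grafted area | No, controls have no graft | 2.1, 2.6 |

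The rule in section 2.10 can therefore be carried out for two of the four items.

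**Step 3. How far complete-case analysis could move the collapse-length difference.** Assumptions:
- There are 25 matched pairs (the enrolment target; the caliper may leave fewer).
- Converted hips would have shown *d* mm more collapse than unconverted ones, with the same *d* in both groups.
- The matched partner of a converted hip is typical of its own group.

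Let *f* be the share converted. The complete-case mean in a group falls short of the mean over all hips by *f* × *d*. In the difference, treatment minus control, this gives

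shift = -(f_treatment - f_control) × d.

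A positive shift makes treatment look worse, a negative one better.

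| Converted, treatment vs control (of 25) | d = 1 mm | d = 3 mm | Complete pairs left |
|---|---|---|---|
| 1 vs 3 | +0.08 | +0.24 | 21 to 22 |
| 2 vs 5 | +0.12 | +0.36 | 18 to 20 |
| 2 vs 8 | +0.24 | +0.72 | 15 to 17 |
| 4 vs 4 | 0 | 0 | 17 to 21 |
| 5 vs 2 | -0.12 | -0.36 | 18 to 20 |
| 8 vs 2 | -0.24 | -0.72 | 15 to 17 |

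Example: 2 vs 8 with d = 3 gives -(0.08 - 0.32) × 3 = +0.72 mm. The pairs left are 25 - (2 + 8) = 15 if no pair has two conversions, and 25 - 8 = 17 if both treated conversions fall in pairs whose control also converted.

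**The case against.** The contradiction over group comparisons is narrow. The Discussion contains the specific rule for HHS and JHEQ and gives the reason; section 2.10 is a generic sentence. CT of the grafted area is within-group by its own definition. This stands, and reduces that part to aligning the wording of section 2.10.

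Failures are not hidden, because THA counts in the primary outcome, and collapse length is also measured at 3 and 6 months. That is true, but it does not repair the 12-month comparison.

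Handling of THA in secondary outcomes could be left to an analysis plan that is not shown. For the hip scores this stands, because the article is silent. For collapse length it does not: the article itself fixes complete-case analysis and excludes sensitivity analyses, so an analysis plan would have to override it.

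A reader might go further and infer that hip scores are inflated: the Introduction says that THA "provides excellent pain relief and functional outcomes", so a converted patient's good 12-month score would count as benefit, while dropping that patient would also flatter the result. The documents do not support this. No text says that scores after THA will be used, or that THA ends participation. Table 1 has a discontinuation visit with a questionnaire, but the text does not say whether THA triggers it. The Introduction's remark gives no score and no timing. Whether leaving converted patients out flatters the result depends on the value one chooses to assign to a failure. Any effect would fall on a within-group description, not on the treatment contrast.

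**Conclusion.** The point holds for 12-month collapse length. As written, the plan drops hips because they failed, and nothing planned would show the consequence. That follows from the definition of the measure and the complete-case rule alone.

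The size and direction are not known. The range of -0.72 to +0.72 mm rests wholly on assumed conversion counts and assumed excess collapse. A reader might infer that hips are lost unequally by group, or that the rule favours the new treatment. The documents give no THA rates and support neither. If controls convert more often, the rule works against treatment. If conversion rates and excess collapse are equal, the difference is unbiased, although pairs are still lost.

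The primary outcome is not affected. The mismatch on group comparisons is real for HHS and JHEQ, and by implication for CT remodeling, but it is a matter of wording. It does not extend to radiographic progression or collapse length. For hip scores after THA, only an open question about reporting remains.

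**What to change.** Amend section 2.10 as follows.

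1. Compare 12-month collapse length as an ordered outcome with THA ranked worst, using a rank-based method that respects the matching. A pair with one converted hip is then ordered against that hip, and a pair with two is a tie. Report mm change in unconverted hips as supportive, and give the number converted in each group.
2. Name radiographic progression and collapse length as the only secondary outcomes compared between groups. State that HHS, JHEQ and CT remodeling of the grafted area are within-group and descriptive, in line with the Discussion.
3. Report HHS and JHEQ together with the number of THA conversions, and show scores before THA separately from any scores after it.

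Multiple imputation would not serve for item 1, because the value does not exist after THA.

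The cost is a few sentences and no new data. The downside is that a rank-based result is slightly harder to read than a mean change in mm; the supportive summary in unconverted hips keeps the mm scale available.

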### 2.11. Safety Assessment

All adverse events (AEs) occurring after surgery will be recorded regardless of causality, with pre-existing conditions excluded unless worsened. AEs will be collected from the time of surgery, with all procedure- and device-related events recorded within 4 weeks and only device-related AEs and serious adverse events (SAEs) thereafter. SAEs, defined as events that are fatal, life-threatening, require hospitalization, or result in disability, will be reported promptly and managed according to institutional regulations. Potential risks include local reactions at the implantation site, delayed healing, and general perioperative complications such as bleeding, infection, nerve injury, and thrombosis. All procedures will be performed using standard sterile techniques to minimize risk, and the study will be suspended if significant safety concerns arise.

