
The aim of this study is to evaluate the efficacy and safety of arthroscopy-assisted core decompression combined with OCP/Gel implantation for patients with osteonecrosis of the femoral head. Specifically, this study will assess its potential to promote bone regeneration and prevent femoral head collapse, while enabling the simultaneous evaluation and treatment of intra-articular pathology.

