### 2.8. The Study Procedure and Schedule

The study procedures and schedule are summarized in Table 1, in accordance with the SPIRIT recommendations. Eligible patients will be identified during outpatient visits. After a detailed explanation of the study, written informed consent will be obtained. Participants may withdraw their consent at any time without any consequences. Following consent, screening assessments will be performed within 1 month prior to surgery. Baseline data, including demographic characteristics (age, sex, height, and weight), medical history, and comorbidities, will be collected from medical records. Eligibility will be confirmed, and patient registration will be completed before surgery. All enrolled patients will undergo the surgical procedure as described above. Postoperative follow-up assessments will be conducted at 1 week, 4 weeks, 3 months, 6 months, and 12 months after surgery. Radiographic evaluation using X-rays will be performed at baseline and at each follow-up visit. Computed tomography (CT) will be performed at baseline and during follow-up to assess bone remodeling. Clinical laboratory tests will be conducted at baseline and during the early postoperative period. Vital signs, including blood pressure, pulse rate, body temperature, and respiratory rate, will be monitored during hospitalization and the immediate postoperative period. Patient-reported outcomes, including the HHS [42] and JHEQ [43], will be assessed at baseline, 3 months, and 12 months. Adverse events will be monitored throughout the study period regardless of their causal relationship with the intervention. Rehabilitation will be initiated during hospitalization and continued after discharge according to the patient’s weight-bearing status. Postoperative rehabilitation will generally be performed once daily during hospitalization and approximately once weekly until 6 weeks after surgery, with further adjustments as clinically indicated. Patients will remain non-weight-bearing for 3 weeks after surgery, followed by gradual progression to weight-bearing according to clinical symptoms and radiographic findings. Information on concomitant medications, including corticosteroids, immunosuppressive agents, and osteoporosis treatments, will be collected from baseline until the end of follow-up.

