
## Figures and Tables

**Figure 1 medsci-14-00339-f001:**
[figure not shown]
Study flowchart. Patients with ONFH are prospectively enrolled and undergo arthroscopy-assisted core decompression combined with OCP/Gel implantation. Outcomes are compared with a propensity score–matched historical control cohort.

**Table 1 medsci-14-00339-t001:** Schedule of enrollment, interventions, and assessments (SPIRIT).

	Outpatient Evaluation Before Intervention			In-Hospital	Outpatient/In-Hospital Evaluation					
	Obtain consent	Screening	Enrollment	Intervention	1 week	4 week	3 months	6 months	1 year	discontinuation
Allowance duration	−2 months to screening	−2 months ± 2 week	Screening to day before intervention	± 0 day	± 1 days	± 1 week	± 2 week	± 2 week	± 2 week	―
Obtain consent										
Research participant background ^a^		●								
Enrollment			●							
Intervention				●						
X-rays		●		●	●	●	●	●	●	●
CT		●					●		●	●
Vital check				●	●					
Blood test ^b^		●		●	●					
Questionnaire			○				○		○	○
Adverse events ^c^										
Physical therapy ^d^										●
Concomitant medication ^e^										●

● indicates a medically required item, and ○ indicates a required item added for research purposes. a: Age, sex, height, weight, medical history, and comorbidities. This information is collected from the medical record. b: White blood cell count, red blood cell count, Hb, Ht, PLT, TP, ALB, T-BIL, AST, ALT, BUN, Cre, Na, K, Cl, LDH, ALP, CRP. c: Adverse events refer to all undesirable occurrences, such as side effects, and do not necessarily have a causal relationship with the research. d: During hospitalization, the procedure will be performed once a day. After discharge, depending on the patient’s ability to bear weight, it will be performed approximately once a week for the first six weeks post-surgery, and if necessary, approximately three months after discharge. e: Data will be collected only for steroids, immunosuppressants, and osteoporosis medications, from registration to the end of treatment. ➡ indicates the sequence or progression from one study phase/time point to the next.

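### Section 2.11 gives two incompatible rules for recording adverse events; under the narrower one, some non-serious events can go unrecorded, mainly after week 4

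*Protocol article*

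**What the plan says.** Safety is part of the study's purpose. The Introduction states "The aim of this study is to evaluate the efficacy and safety of arthroscopy-assisted core decompression combined with OCP/Gel implantation".

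The article describes adverse events in three places:

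- **Section 2.11, first sentence:** "All adverse events (AEs) occurring after surgery will be recorded regardless of causality". It excludes pre-existing conditions unless they worsen and sets no end date.
- **Section 2.11, second sentence:** collection starts at surgery, "with all procedure- and device-related events recorded within 4 weeks and only device-related AEs and serious adverse events (SAEs) thereafter".
- **Section 2.8:** "Adverse events will be monitored throughout the study period regardless of their causal relationship with the intervention".

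Footnote c of Table 1 adds a definition: "Adverse events refer to all undesirable occurrences, such as side effects, and do not necessarily have a causal relationship with the research". Section 2.11 then defines serious events, "SAEs, defined as events that are fatal, life-threatening, require hospitalization, or result in disability", and requires that they be reported promptly. Among the potential risks it names "delayed healing, and general perioperative complications such as bleeding, infection, nerve injury, and thrombosis".

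**The concern.** A rule that takes every event whatever its cause, and a rule that after week 4 takes only device-related or serious ones, cannot both be applied to the same patient. Whoever completes the case report form at 3, 6 or 12 months has to choose between two adjacent sentences.

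At stake is the completeness of the non-serious safety data. Under the narrower sentence, a non-serious nerve symptom or slow healing that is first noted after week 4 and put down to the procedure, not the graft, need not be entered, although the same section names both kinds of problem as risks. Attribution also becomes a condition for recording, when it could be an attribute of a recorded event. In a single operation that combines arthroscopy, traction, drilling and grafting, the device and procedure contributions may be hard to separate. Events not entered at the time may not be recoverable later, and the study is meant to inform larger trials.

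**Working it through.** The plan gives no figure to reproduce. The check sets the two sentences of section 2.11 side by side, class by class.

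| Event class | First sentence of 2.11 | Second sentence of 2.11 |
|---|---|---|
| Procedure- or device-related, within 4 weeks | recorded | recorded |
| Unrelated and non-serious, within 4 weeks | recorded | not listed |
| Device-related, after week 4 | recorded | recorded |
| Serious, any cause, after week 4 | recorded | recorded |
| Procedure-related, non-serious, not attributed to the device, after week 4 | recorded | not recorded |
| Unrelated and non-serious, after week 4 | recorded | not recorded |

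The sentences agree on three classes and disagree on three, and every disagreement concerns non-serious events. An unrelated serious event within 4 weeks is not named in the second sentence. The separate requirement to report serious events promptly carries no time limit, so it is taken as captured.

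**Can the second sentence be a refinement of the first?** No. Applied as a refinement, it removes both the completeness and the indifference to cause that the first sentence promises.

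**Do other sections settle it?** Section 2.8 covers the whole study period without regard to cause, which supports the broader rule, but it speaks of monitoring and not of recording. Footnote c defines an adverse event without requiring a causal link but sets no recording rule. The adverse-event row of Table 1 shows no readable marks in the text available, so it neither confirms nor resolves the conflict.

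**How much of follow-up is affected?**

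- Follow-up: 12 months, about 52 weeks (section 2.8).
- End of the fuller window: week 4 (section 2.11).
- Time under the narrower tier: 52 − 4 = 48 weeks; 48/52 = 0.923, about 92%.
- Visits: "Postoperative follow-up assessments will be conducted at 1 week, 4 weeks, 3 months, 6 months, and 12 months after surgery". Three of the five (3, 6 and 12 months) fall in the narrower tier.

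The 92% is a share of calendar time. The article gives no timing for procedure-related events, so it cannot be read as a share of expected events.

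**The case against.** The strongest reply is that tiered collection is a legitimate choice for a device that already has regulatory approval and insurance coverage in Japan (section 2.5), and that the loss is small. Much of this stands. Serious events and device-related events are kept under both rules. Perioperative complications such as nerve injury may well begin inside the 4-week window, where the narrower rule takes all procedure-related events. Delayed healing may be judged device-related and so remain recordable. Pain and function are partly covered by the Harris Hip Score and the JHEQ at 3 and 12 months, and imaging continues through follow-up. Section 2.8 can also be read as monitoring everything while recording in tiers. None of this removes the clash inside section 2.11, where both sentences are about recording.

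Three stronger readings are tempting, and the documents do not support them:

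- A reader might infer that different sites would produce different safety tables. The trial is single-center (section 2.1); at most, different staff could apply different sentences.
- A reader might infer that an uncollected class will be reported as 0 of 25 with an exact upper 95% limit of 1 − 0.025^(1/25) = 13.7%. The arithmetic is right, but the article plans no such report, and a safety table can state its collection window.
- A reader might infer that this is the first use of the combined procedure, which would raise the stakes. The article calls the approach novel and does not say it is the first use.

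**Conclusion.** Section 2.11 contradicts itself on which adverse events are recorded, and no other part of the article resolves it. The contradiction lies in what is written, so it is not a detail left to a fuller document.

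Its reach is limited to non-serious events: those after week 4 not attributed to the device (about 48 of 52 weeks), and unrelated ones in the first 4 weeks. The loss is conditional, because it occurs only if the narrower sentence is the one followed, and the article does not show which is intended. How many events would be lost cannot be estimated from the article.

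The primary outcome is unaffected. This should be fixed, because safety is a stated aim and the correction is cheap, but it does not undermine the trial.

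**What to change.** Reconcile sections 2.8 and 2.11 into one data-recording rule.

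- **Preferred:** keep the rule in the first sentence of 2.11, stated explicitly as all adverse events from surgery to the 12-month visit. Record relatedness to the procedure and to the device as two separate attributes, and remove the 4-week restriction. This agrees with section 2.8 and with footnote c of Table 1.
- **If the sponsor keeps the tiered rule:** remove the all-events, any-cause wording from 2.11, align 2.8 with it, and state the collection window with every safety result, so that readers know which non-serious events were not sought.

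The cost is one sentence and one case report form instruction. The visits already exist. Under the preferred option the downside is somewhat more non-serious events to enter for 25 patients.
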